## Abstract

**Background:**

Abdominal pain is a common reason for children to attend the Emergency Department (ED) with acute appendicitis being the most common surgical cause. Various clinical prediction scores (CPSs) have been developed to assist in determining the risk of appendicitis; however, CPSs have been inadequately validated in children and haphazardly adopted in Australia and New Zealand (ANZ) EDs.

**Objective:**

This study aims to compare and validate various CPSs for diagnosing pediatric appendicitis in children presenting to ANZ EDs.

**Methods:**

This prospective multicenter observational study across 10 ANZ EDs is recruiting children 5-17 years presenting to participating EDs with acute right-sided or generalized abdominal pain lasting ≤7 days and clinician suspicion of appendicitis. CPSs will be calculated by the study team from clinician-recorded data and clinician gestalt recorded on a visual analog scale. Accuracy of CPSs will be assessed by the area under the receiver operating characteristic curve and proportions correctly identified as either low-risk or high-risk based on the CPSs published cutoffs. The final diagnosis of appendicitis will be confirmed on histopathology, and the absence of appendicitis confirmed by telephone, email, or a combination of both to follow up for those discharged directly from ED.

**Results:**

This study received funding in July 2023 and started enrolment in August 2023. As of October 2024, we have enrolled and completed follow-up on 1227 participants with an expected end date in mid-2025.

**Conclusions:**

This study aims to determine the best-performing CPS for diagnosing pediatric appendicitis in ANZ EDs. Implementation of this CPS in ANZ EDs has the potential to reduce health care costs, rationalize the use of health care resources, and improve the management and outcomes of childhood appendicitis.

**Trial Registration:**

Australian New Zealand Clinical Trials Registry ACTRN12622001293752; https://tinyurl.com/242wwenx

**International Registered Report Identifier (IRRID):**

DERR1-10.2196/67941

## Introduction

### Background

Abdominal pain is a common reason for children to attend the emergency department (ED), with acute appendicitis being the most frequent cause requiring surgical intervention [1]. Many clinical prediction scores (CPSs) [2-31] have been developed and ED clinicians are encouraged to use CPSs to assist with determining the risk of appendicitis [32]. Most CPSs involve calculating a score based on combinations of clinical features and laboratory findings to classify patients into low-, intermediate-, or high-risk. The most frequently used CPSs in children are the Alvarado score [2], the Pediatric Appendicitis Score (PAS) [3], and the pediatric appendicitis risk calculator (pARC) [4], with each based on different sets of collected variables.

The Alvarado score is one of the most widely studied CPSs for the diagnosis of acute appendicitis in adult populations based on 8 variables with a total score of 10 [2], and it has since been studied in pediatric populations with varying results [33-44]. The PAS was developed specifically with slightly different variables for diagnosing appendicitis in children [3] and has been validated in multiple studies in various settings [42-54]. However, both the Alvarado score and PAS have been found to have limited clinical utility due to a large proportion of the scores falling into the intermediate risk group and failing to consider variability in clinical presentation based on factors such as age, sex, and duration of pain. This led to the development of the pARC score, which uses a multivariable prediction model that includes variables such as age, sex, and duration of pain to quantify the risk of appendicitis on a continuous scale [4], with promising results noted on various validation studies since its development [36,43,44,55-57].

However, few have compared multiple CPSs for pediatric appendicitis, and most existing studies are limited by the number of CPSs included [36,40,58], validated only in retrospective cohorts [59], did not include more recent CPSs such as the pARC score [40,59,60], and did not compare CPSs to clinician gestalt. Moreover, most of these studies were performed overseas with limited validation in children in Australia and New Zealand (ANZ) EDs [61]. This can result in inconsistent practice and an increasing number of children exposed to potentially unnecessary imaging and laboratory investigations.

### Objectives

The primary aim of the study is to externally validate various published CPSs for the risk of appendicitis in children aged 5 to <18 years presenting to ANZ EDs with acute abdominal pain and suspicion of appendicitis.

The secondary aims of the study are as follows:

1. To evaluate and compare the performance of various published CPSs:

(A) against clinician gestalt in ANZ for the likelihood of appendicitis at the time of ED assessment;

(B) in identifying, prospectively, the likelihood of complex appendicitis (defined as the presence of perforation, extraluminal fecalith, diffuse intraperitoneal pus, or a well-formed abscess) [62];

2. To describe the epidemiology and management of pediatric appendicitis, illustrating:

(A) The burden of disease in patients presenting with acute abdominal pain with the suspicion of appendicitis;

(B) The incidence and type of surgical procedures undertaken in the management of appendicitis in ANZ (laparoscopic appendectomy, open appendectomy, nonsurgical management with intravenous antibiotics, and delayed appendectomy);

(C) The imaging procedures undertaken in patients assessed for possible appendicitis, and their accuracy in the detection of histologically confirmed appendicitis or surgically confirmed appendicitis in cases where histopathological findings are unavailable.

This will improve the accuracy of diagnosis, reduce health care costs, rationalize the use of health care resources, and improve the management of childhood appendicitis. It will also provide a description of the current diagnostic and management approaches in ANZ for pediatric abdominal pain and appendicitis.

## Methods

### Overview

The study is an endorsed Paediatric Research in Emergency Departments International Collaborative (PREDICT) network [63] study with Perth Children’s Hospital (PCH) as the lead site. The study is a quantitative multicenter observational study that measures the performance accuracy of CPSs in identifying surgically or histologically confirmed appendicitis. Eligible CPSs (Multimedia Appendix 1) were identified in a rapid review by the study authors before study commencement [43]. Any CPS developed in either pediatric or adult populations was eligible except for: CPSs aiming only to differentiate simple from complex appendicitis or performed only for a subset of children (eg, preschool children and children with chronic illnesses); CPSs requiring variables unlikely to be routinely collected in a pediatric population identified a priori through consensus agreement by study authors (eg, rectal examination, biomarkers other than full blood picture, or C-reactive protein); and CPSs that included radiological parameters.

### Study Setting and Population

#### Overview

The study population will be all children presenting to participating ANZ EDs with abdominal pain. Study sites all have EDs that manage pediatric patients and have a pediatric on-site general surgical service with the capacity to provide input, admission, and surgical intervention if needed.

Perth Children’s Hospital (Western Australia, Australia)Children's Hospital Westmead (New South Wales, Australia)Gold Coast University Hospital (Queensland, Australia)Monash Health (Victoria, Australia)Queensland Children's Hospital (Queensland, Australia)Royal Children’s Hospital (Victoria, Australia)Royal Hobart Hospital (Tasmania, Australia)Sunshine Coast University Hospital (Queensland, Australia)Sunshine Hospital (Victoria, Australia)Starship Hospital (Auckland, New Zealand)

#### Participant Inclusion Criteria

To be eligible to participate in the study, a participant must meet the following criteria:

Age 5 to <18 years,Presentation with generalized or right-sided abdominal pain,Duration of pain for ≤7 days (ie, ≤168 h),Clinician’s concern for the possible diagnosis of appendicitis as defined by any one of the following:Investigations performed (blood sample, imaging, or both, including external investigations before ED attendance),Surgical consultation to assess the patient for possible appendicitis,Senior ED clinician consultation to assess the patient for possible appendicitis,Period of observation in ED to reassess patient for possible appendicitis.

For those hospitals with mixed ED and limited pediatric surgical capacity to operate on children under a certain age, the site-specific “pediatric” age range will be applied (eg, >10 years and <16 years). The age range of 5 to < 18 years was chosen due to the rarity and the atypical presentation of appendicitis in younger children [64], and many CPSs required variables on history or examination that might be difficult to determine accurately in younger children. Acute abdominal pain was defined as the duration of pain for ≤7 days in keeping with a previous study looking at abdominal pain and appendicitis [65], and a previous feasibility study found several patients with pain lasting for more than 5 days diagnosed with appendicitis [43].

#### Participant Exclusion Criteria

The following conditions exclude participation in the study:

Abdominal trauma that required medical review within the preceding 7 days,Previous significant abdominal surgery (eg, appendectomy, short gut, ileostomy, and Hirschsprung disease),Chronic illnesses that may affect the abdomen (including inflammatory bowel disease, chronic pancreatitis, cystic fibrosis, and sickle cell anemia),Pregnancy,Inability to obtain accurate history (eg, parent or guardian unavailable, language other than English and where no interpreter was available, or patients who are nonverbal due to pre-existing medical condition).

### Outcome Measures

#### Overview

The primary outcome is the presence of appendicitis; this will be confirmed through the histopathology report when available, or the operation report if not available. Patients diagnosed with appendicitis but managed nonoperatively will be followed up to confirm the presence of appendicitis in cases where interval appendectomy was performed or excluded from analysis in cases treated conservatively with antibiotics only. A nonappendicitis diagnosis will be confirmed on follow-up via either recording of the primary diagnosis on hospital discharge if admitted to hospital, or contact at 30-60 days to ensure no progression in symptoms or representation to hospital for those discharged directly from the ED. The area under the receiver operating characteristic (ROC) curve (AUC) will be calculated for the various published CPS for the primary outcome of appendicitis.

Secondary outcomes include rates of uncomplicated and complicated appendicitis (defined as the presence of perforation, extraluminal fecalith, diffuse intraperitoneal pus, or a well-formed abscess) [62], negative appendectomy cases (based on histopathological findings), and missed appendicitis cases. These will be confirmed through the histopathology report when available, and the operation report if not available. To identify missed appendicitis cases, families of children who did not undergo appendectomy and were discharged directly from the ED will be contacted within 30-60 days of hospital discharge to assess for postdischarge status and whether their child had an appendectomy in the interim. For families unable to be contacted, medical records will be reviewed at 60 days to assess for representation. Other secondary outcome measures include length of hospitalization, rates of investigations, and rates of interventions.

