demographic data (sex and age),eligibility (inclusion and exclusion criteria),caregiver verbal consent,the clinician's seniority and their perceived likelihood of appendicitis on a Visual Analog Scale from 0 being “Extremely unlikely” to 10 being “Extremely likely” and whether this perceived likelihood was formed before or after investigations (bloods, imaging, or both),history of the presenting complaint (location of initial pain, duration of pain, highest pain score, highest reported temperature during this illness, right lower quadrant (RLQ) or right iliac fossa (RIF) pain on arrival to ED, pain migration to RLQ or RIF, progression of pain, gradual onset of pain, pain pattern, history of pain with walking, anorexia, nausea, vomiting, difficulty with micturition, pothole tenderness, family history of appendicitis, respiratory tract infection in last 2 weeks, and bowel habit), andexamination findings (RLQ tenderness, RIF tenderness, tenderness worst in RLQ, tenderness outside RLQ, presence of hop, cough, or percussion tenderness, degree of rebound tenderness, abdominal guarding, Rovsing sign, nature of bowel sounds, palpable abdominal mass, and abdominal rigidity).

Clinician management will proceed independently of study participation.

All data collected at sites will be transcribed to a REDCap (Research Electronic Data Capture; Vanderbilt University) database [66]. The following additional data will be collected from the patient's medical records: blood test results (white cell count, absolute neutrophil count, neutrophilia, and C-reactive protein), urinalysis (presence of leukocytes or nitrites), which will then allow the various CPSs to be automatically calculated in REDCap.

Between 30-60 days after the ED visit, the site research team will collect the following parameters in all eligible patients through a medical record review:

detailed demographics (postcode, Medicare status, race or nationality, and referral source),prehospital management,management and imaging were undertaken both pre-ED in the community and the study hospital,time-related data (times of triage, clinician evaluation, ED, and hospital discharge),duration of ED and hospital stay,admission status and specialty unit consultations, including intensive care admission,medication use in ED, including antibiotics and analgesia,related surgical and nonsurgical interventions,other significant pathology or adverse events, including mortality, anddisposition.

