### Statistics and Interim Analysis

We will follow Standards for the Reporting of Diagnostic accuracy studies (STARD) 2015 guidelines for statistics [69] and the Strengthening the Reporting of Observational Studies in Epidemiology (STROBE) guidelines [70], and validation of CPSs will be performed and reported in according to the 2014 updated methodologic standards for interpreting clinical decision rules in emergency medicine [71]. The AUC will be calculated for the various published CPSs and the clinician's gestalt for the outcome of appendicitis. The sensitivity, specificity, negative predictive value, positive predictive value, negative likelihood ratio, positive likelihood ratio, and missed appendicitis rate will be calculated based on the published cutoffs for each score [2-31]. For the pARC, subanalysis will be performed for the following pARC categories based on previous validation studies [4,56]: ≤5%, 6%-15%, 16%-25%, 26%-50%, 51%-75%, 76%-90%, and >90% for pediatric EDs and <5%, 5%-14%,15%-24%, 25%-49%, 50%-74%, 75%-84%, and ≥85% for mixed ED. For clinician’s gestalt, subanalysis will be performed for each point on the Visual Analog Scale. The AUC will also be calculated for complex appendicitis to assess the optimal cutoffs for each CPS to detect complex appendicitis.

The best-performing CPS will be identified by the highest AUC. Sensitivity and positive predictive value will be calculated to establish the CPS’s ability to identify high-risk patients, and the misclassification rate (proportion of patients identified as low-risk who had acute appendicitis) and negative likelihood ratio will be calculated to establish the CPS’s ability to identify low-risk patients. Accuracy will be reported as the proportion of patients not misclassified as either low-risk or high-risk as defined by published cutoffs. Baseline analyses of patient characteristics based on the risk groups as calculated by the best-performing CPS will be conducted by presenting simple counts and percentages with interquartile ranges.

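### Complicated appendicitis is sourced from histopathology first, although a specimen report cannot reliably establish three of its four defining criteria

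*Protocol article*

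**What the plan says.** The Protocol article (Outcome Measures, Overview) lists complicated appendicitis among the secondary outcomes, "defined as the presence of perforation, extraluminal fecalith, diffuse intraperitoneal pus, or a well-formed abscess". Any one of the four is enough. The same paragraph then names the source for the listed outcomes: "These will be confirmed through the histopathology report when available, and the operation report if not available". The primary outcome, appendicitis yes or no, has the same order of sources: "this will be confirmed through the histopathology report when available, or the operation report if not available".

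The label is used in three places:

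- the rates of uncomplicated and complicated appendicitis (Outcome Measures);
- aim 1(B) in Objectives, which evaluates the scores "in identifying, prospectively, the likelihood of complex appendicitis";
- Statistics and Interim Analysis: "The AUC will also be calculated for complex appendicitis to assess the optimal cutoffs for each CPS to detect complex appendicitis".

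The record-review list in Patient Recruitment and Data Collection includes "related surgical and nonsurgical interventions" and does not name operative findings.

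**The concern.** The definition and the source rule do not fit together. A histopathology report describes the tissue that was removed. Of the four criteria, only perforation is a feature of that tissue. The other three describe the peritoneal cavity, and the document that records them is the operation report. Under the stated rule that report is used only where histopathology is not available.

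What triggers the fallback is whether a histology report exists, not whether it can answer the question. If the rule is applied as written, the working definition of complicated appendicitis shrinks towards perforation seen on the specimen. Complex cases then move into the uncomplicated group and none move the other way, so the complicated rate is biased downward. The cutoffs sought for the 30 scores would be fitted to a narrower outcome than the one the protocol defines, and a larger sample would not correct this.

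**Working it through.** **1. The rule applied to the possible cases.** Take a child with appendicitis who had an operation.

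- Histology report exists and shows perforation: complex by definition, complex by rule.
- Histology report exists and shows no perforation; operation report records diffuse pus, an abscess or an extraluminal fecalith: complex by definition, uncomplicated by rule unless the pathologist happens to mention the finding.
- Histology report exists; neither report records a criterion: uncomplicated by both.
- No histology report: the operation report is read, and rule and definition agree.

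Only the second kind of case is miscoded.

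**2. Whether another section repairs it.** Aim 2(C) in Objectives uses the same order, with surgical confirmation standing in where histology is lacking. No section says that both reports are read together for complexity.

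**3. The plan's own sizing figure.** Sample Size and Power Calculation gives 2400 children, 30% with appendicitis, and all scores calculable in at least half.

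- Cases: 2400 × 0.30 × 0.50 = 360. Non-cases: 2400 × 0.70 × 0.50 = 840. The stated 360 is reproduced.
- The Hanley–McNeil standard error, SE² = [A(1−A) + (n₁−1)(Q₁−A²) + (n₀−1)(Q₂−A²)]/(n₁n₀) with Q₁ = A/(2−A) and Q₂ = 2A²/(1+A), gives 1.96 × 0.00819 = 0.016 at A = 0.95 and 1.96 × 0.01637 = 0.032 at A = 0.75. Both stated values are reproduced, as half-widths.

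These figures concern appendicitis yes or no and do not change. No figure is stated for complex appendicitis.

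**4. Illustration of the miscoded count.** The complicated rate uses all appendicitis cases, not only those with every score calculable: 2400 × 0.30 = 720. Let q be the share truly complex and s the share of those recognisable on histology. Neither is in the documents; q = 0.20–0.40 and s = 0.50–0.90 are assumptions. A histology report is taken to exist for every case, which is also an assumption; if only a share h has one, multiply the count by h.

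- Miscoded = 720 × q × (1−s). Smallest: 720 × 0.20 × 0.10 = 14.4. Largest: 720 × 0.40 × 0.50 = 144.
- Observed complicated rate = q × s, which runs from 0.20 × 0.50 = 10% to 0.40 × 0.90 = 36%, where the true rate is 20–40%.
- Truly complex share of the group labelled uncomplicated = 720q(1−s)/(720 − 720qs). Smallest: 14.4/590.4 = 2.4%. Largest: 144/576 = 25%.

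Among the 360 fully calculable cases the counts halve, to about 7 to 72.

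**5. Illustration of the AUC effect.** Suppose missed complex cases score like detected ones. Contamination c of the comparison group then lowers a true AUC of A by c × (A − 0.5). The article does not say which comparison group is meant.

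- Uncomplicated cases only, A = 0.70 assumed: 0.024 × 0.20 = 0.005 to 0.25 × 0.20 = 0.050.
- All other children, A = 0.85 assumed: c = 14.4/(2400 − 129.6) = 0.6% to 144/(2400 − 144) = 6.4%, so the loss is 0.002 to 0.022.

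If missed cases score differently from detected ones, the size changes and the direction is no longer fixed. Only the bias in the rate has a certain direction.

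**The case against.** The strongest reply is that the fallback can be read more kindly: the operation report is used where the needed finding, and not the document, is unavailable from histology. Aim 2(C) does speak of findings. But the sentence that governs this outcome names the report, so the kinder reading is what the protocol should say and not what it says.

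A second reply is that the harm is limited, and this largely stands. The primary aim, the choice of the best score by highest AUC, and the sample size all rest on appendicitis yes or no, for which histopathology first is a sound rule. The AUC losses illustrated above are small over much of the range. Operation reports are already a named source, so the label may be recoverable before analysis. The full protocol and data dictionary, where criterion-level coding might sit, are not shown; for that reason the absence of operative findings from the article's list is not counted as an error in itself.

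Three stronger readings are tempting, and the documents do not support them.

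- A reader might infer that the three criteria can never appear on a histology report. A pathologist may describe an abscess around the appendix or repeat details from the request form. What holds is that such a report cannot be relied on to establish them.
- A reader might infer that the operation report would almost never be consulted, because nearly every appendectomy yields histology. That is plausible, but the article gives no such figure.
- A reader might infer that an operation report may stand in for histology in negative appendectomy. The article ties that outcome specifically to histopathological findings, and the specific wording governs the general sentence.

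**Conclusion.** The point holds as a wrong source rule for one secondary outcome. If it is followed literally, cases whose only qualifying criterion was seen at operation are coded uncomplicated whenever a histology report exists. The complicated rate is then understated, and the aim 1(B) AUCs and cutoffs are estimated against a mislabelled outcome.

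The documents do not determine the size. The range of about 14 to 144 of 720 rests wholly on the assumed complex share, the assumed share recognisable on histology, and a histology report for every case; its width shows how little can be said. The conclusion itself rests only on the definition and the rule standing together in one paragraph. Severity: should be fixed. It is not critical, because the primary outcome and everything sized on it are unaffected.

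**What to change.** Separate the source rules in Outcome Measures:

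- Appendicitis yes or no, and negative appendectomy: histopathology first, as now.
- Complicated appendicitis: present if any of the four criteria is recorded in either the operation report or the histopathology report.

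Record the four criteria as individual data items at the 30–60 day record review, each with its source, so that the label can be checked and rebuilt.

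The cost is one sentence, four data fields and a little more abstraction from a source already named. For the 1227 participants already followed up by October 2024, the reports may have to be read again; at the assumed 30% rate that is about 1227 × 0.30 ≈ 368 children with appendicitis. Identifiable data leave the REDCap database at 61 days after enrolment, which may make later re-abstraction harder, so the change is cheaper the sooner it is made.
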